**Table 1 Tab1:**
[figure not shown]
Schedule of enrollment, interventions and assessments for TRADE study

Legend: *-marked items will only be conducted in interventional part, *^2^-marked items will only be conducted in observational part. Charlson Comorbidity Index (CCI), Patient Health Questionnaire 4 (PHQ-4), Numeric Rating Pain Scale (NRS)*, Pittsburgh Sleep Quality Index (PSQI), Simplified nutritional appetite questionnaire (SNAQ), Mini Nutritional Assessment-Short Form (MNA-SF)*, Lubben-6 Social Network Skala (LSNS-6), Clinical Frailty Scale (CSHA), Informant Questionnaire on Cognitive Decline (IQCODE), Delirium risk factors (including alcohol, history of falls, sensory impairment, subjective cognitive decline, pain, history of delirium), ICD-10 supplemented Confusion Assessment Method Severity Score (I-CAM-S), 3-Minute Diagnostic Interview for Confusion Assessment Method defined Delirium (3D-CAM) *, Bedside Confusion Scale (BCS)*, Montreal Cognitive Assessment (MoCA), Nurses Delirium Rating Scale (Nu-DESC), Single Question in Delirium (SQiD) with Nurse and Caregiver*, Family-Confusion Assessment Method (FAM-CAM), Barthel Index (BI), Instrumental Activities of Daily Living (IADL)

### Participant ‘s timeline

From the participant’s perspective the study starts in the hospital with a detailed baseline assessment four/three days or less prior to discharge (T0). After discharge follow-up assessments are on day 3 (+/− 1 day; T1), on day 7 (+/− 1 day; T2) and day 90 (+/− 7 days, T3). While in the observational study all visits were done personally, for the pilot intervention a telephone assessment with the primary caregiver replaces the personal visit at T1 in order to reduce patient contacts because of the SARS-CoV2-pandemic. For T2 and T3, participants are still visited in the respective discharge environment. If facilities do not allow personal visits, a full telephone-based follow-up visit (T1-T3) will be performed.

Primary caregivers are interviewed at each follow-up timepoint (T1, T2, T3) by phone. Attending nurses are interviewed at each follow-up and baseline assessment personally or by phone (T0, T2, T3).

The study timeline is summarized in Fig. 4.

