## Background

Delirium is a growing medical burden especially for hospitalized older adults with incidences of up to one third among those 70 years of age or older [1]. In a meta-analysis with 42 studies delirium in hospital and post-acute care was associated with increased post discharge mortality and institutionalization rates [2]. Risk factors for delirium are multidimensional and include non-modifiable aspects such as age, acute illness or pre-existing dementia [3]. Others, like major surgery, anesthesia, immobilization during inpatient treatment, drug side effects and several psychological, social and environmental factors are linked to acute hospital care itself and potentially modifiable [4–7]. Delirium is associated with complications such as falls, nosocomial infections and subsequent loss of autonomy. Delirium prevention and treatment is, therefore, an indicator of patient safety and quality in modern health care settings [8, 9].

Most deliria occur during the first days after admission to a hospital. In addition to the acute illness, hospital and room transfers could account as triggers [10]. In retrospective cohort studies room transfers in acute care hospitals have been shown to increase delirium risk in surgical and nonsurgical patients [11, 12]. However, the impact of transportation or transfer within a hospital and/or after discharge has not been evaluated prospectively.

Considering therapeutic and preventive strategies, non-pharmacologic interventions with a focus on reorientation, minimal change in hospital staff and involvement of family caregivers are effective ways to reduce delirium incidence during hospital stay [13]. Potentially modifiable environmental factors such as providing reading glasses and hearing aids or family support can reduce the severity of delirium symptoms in nursing home residents [14]. The most prominent multicomponent non-pharmacologic intervention is the Hospital Elder Life Program (HELP), which reduced in a hospital setting cognitive decline from 26 to 8% and functional decline from 33 to 14% in a cohort of older persons [15]. A meta-analysis of 14 interventional studies showed that a multicomponent intervention including changes in environmental factors was associated with a significant risk reduction for incident delirium of 0.53 (95% confidence interval (CI) 0.38 to 0.58) [16].

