#### Delirium

When screening for delirium, anamnestic information on acute onset and fluctuating course is essential for delirium detection, but can be difficult to acquire in a single contact with the participant. Therefore, delirium screening strategy in TRADE combines information from different sources: patient, caregiver, and nurse. Delirium is screened by interviewing the patient, the primary caregiver and the nursing staff at baseline and on day 3, 7 and 90 after discharge. In the intervention part of the study delirium screening on day 3 after discharge will only be performed in a telephone interview with the primary caregiver.

As main delirium screening tool for assessing the patient the German version of the Confusion Assessment Method (CAM) is being used [26, 27]. This gold standard of delirium detection has been adapted over time to several sub-assessments preserving the four key elements in detecting inattention, disorganized thinking, alteration of consciousness and acute onset/ fluctuating course. In the observational cohort study we use the I-CAM-S Version combining a double check with ICD-10 criteria (I-CAM) and a delirium severity score (CAM-S) as described by Sánchez et al. [7, 28, 29]. In the interventional part of the study the 3-min diagnostic interview CAM version (3D-CAM) has been added [30]. 3D-CAM facilitates assessment for the raters by detailed instructions and closed questions. For the caregivers the Family Confusion Assessment Method (FAM-CAM) will be used [31]. The five-item Nursing delirium screening scale (Nu-DESC) allows to rate attending nurses’ observations concerning disorientation, inappropriate behavior and communication, hallucinations and psychomotor retardation over a 24-h period [32]. For the interventional part of the study two easy to use screening instruments for delirium were added to the assessment battery: The bedside confusion scale (BCS) as a simple and short test for delirium that can be derived from 3D-CAM assessment and focuses on the items psychomotor disturbance and awareness [33]. In addition, attending nurses and primary caregivers will be asked the *Single Question in Delirium* assessment (SQiD): ‘Do you think [name of patient] has been more confused lately?’ [34].

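### The protocol contradicts itself on whether the caregiver, normally the pilot's only day-3 delirium source, is screened at baseline, so delirium that began in hospital can enter the post-discharge count

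*Protocol article*

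**What the plan says.** Two sections of the protocol article give the schedule of caregiver delirium screening.

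- **Delirium (Primary outcomes).** "Delirium is screened by interviewing the patient, the primary caregiver and the nursing staff at baseline and on day 3, 7 and 90 after discharge". For the pilot, it then says that "delirium screening on day 3 after discharge will only be performed in a telephone interview with the primary caregiver".
- **Participant's timeline.** "Primary caregivers are interviewed at each follow-up timepoint (T1, T2, T3) by phone". The next sentence reads "Attending nurses are interviewed at each follow-up and baseline assessment personally or by phone (T0, T2, T3". For the pilot, "a telephone assessment with the primary caregiver replaces the personal visit at T1". Where facilities bar visits, a full telephone follow-up covering T1 to T3 is done instead.

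The Delirium subsection names the FAM-CAM for caregivers. In the pilot it adds the SQiD for nurses and caregivers, which asks whether the patient "has been more confused lately". The readable text does not say at which visits the SQiD is used. The combined endpoint counts delirium as present once any assessment from any source shows signs of it. No rule for delirium already present before discharge is visible.

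In the pilot, T0 can fall up to three days before discharge (Inclusion criteria), and T1 is day 3 plus or minus one day.

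**The concern.** The endpoint is meant to capture delirium arising with transfer or discharge. For that, each source needs either a reading before discharge or a question that separates the time before discharge from the time after it. On the timeline's wording, the caregiver has no reading before discharge, and the SQiD's recall window does not start at discharge. A caregiver called on day 2 to 4 who saw the patient confused on the ward can truthfully answer yes. Nothing from that caregiver would then show that the confusion began earlier.

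This is not remote, since the Background states "Most deliria occur during the first days after admission to a hospital". The Delirium subsection also concedes that acute onset and fluctuation are hard to establish in one patient contact, so a negative patient test at T0 does not close the question.

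Events carried over in this way would add a similar background rate to control and intervention periods. They would shrink the relative effect of the intervention and overstate the delirium attributed to discharge, which the project also sets out to measure.

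**Working it through.** **1. The schedule, source by source, as the text gives it**

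| Source | Delirium subsection | Participant's timeline (pilot) |
|---|---|---|
| Patient | baseline, days 7 and 90 | T0, T2, T3 |
| Nurse | baseline, days 7 and 90 | T0, T2, T3 |
| Caregiver | baseline, days 3, 7 and 90 | T1, T2, T3; T0 not listed |

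The day-3 entries in the middle column apply the pilot restriction to caregiver-only screening. The two sections agree for patients and nurses and differ on the caregiver at T0. Because the adjacent timeline sentence does name T0 for nurses, the omission is hard to read as shorthand.

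**2. Route to a misclassified event**

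A caregiver report at T1 is normally the only day-3 information, and one positive report suffices for the endpoint. Two kinds of pre-discharge delirium can enter this way: an episode before T0 that the patient and nurse assessments did not record, and an onset between T0 and discharge, a window of up to three days. A caregiver interview at T0 helps with the first. Only dating the onset deals with the second.

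**3. The plan's own power figure**

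Inputs from Sample size: 400 evaluable patients, 6% versus 0.9%, two-sided 5% chi-square test, power at least 80%. The split of 200 per condition is my assumption, as the section does not state it.

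Power = Φ{[√n·(p1 − p2) − 1.96·√(2·p̄·(1 − p̄))] / √(p1(1 − p1) + p2(1 − p2))}, where p̄ is the mean of p1 and p2.

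With n = 200, p1 = 0.06, p2 = 0.009 and p̄ = 0.0345:

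(14.142 × 0.051 − 1.96 × 0.2581) / 0.2556 = 0.843, so power = 80.0%. The stated figure reproduces. So does the enrolment target: 400 / (1 − 0.20) = 500.

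**4. Illustration of carry-over**

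Let c be the share of patients without post-discharge delirium who are counted as cases because of earlier delirium, equal in both conditions. The documents give no value for c. The observed rate is then p + (1 − p)·c. For c = 1%: 0.06 + 0.94 × 0.01 = 6.94% and 0.009 + 0.991 × 0.01 = 1.89%.

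| c (assumed) | Control | Intervention | Difference (points) | Risk ratio | Power |
|---|---|---|---|---|---|
| 0 | 6.00% | 0.90% | 5.10 | 0.15 | 80% |
| 1% | 6.94% | 1.89% | 5.05 | 0.27 | 69% |
| 2% | 7.88% | 2.88% | 5.00 | 0.37 | 60% |
| 3% | 8.82% | 3.87% | 4.95 | 0.44 | 53% |

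The absolute difference hardly moves. The loss comes from the higher background rate, which pulls the relative effect towards no effect and raises the variance. The planned model for binary outcomes uses a logit link, so the relative scale is the one estimated. At c = 1%, even an intervention that prevented every post-discharge case would leave an observed rate of 1.0%, above the 0.9% used in the power statement.

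**The case against.** The strongest reply is that the missing caregiver baseline is inferred. The timeline sentence describes follow-up calls and how they are made; it does not say that caregivers are not interviewed at T0. The Delirium subsection says that they are, and caregiver participation is mandatory in the pilot. Table 1 and Fig. 4, whose legend lists T0 to T3 with time per assessed group including caregivers, are not readable here and may show the contact. This stands: a reader might infer that the protocol omits the caregiver baseline, but the documents support only a conflict between two sections.

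Other parts of the reply also stand:

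- SQiD use at T1 is not stated, and no recall problem is shown for the FAM-CAM.
- Patients and nurses are assessed at T0, the nurses with a scale covering 24 hours, so some prevalent cases will be recognised. Episodes already resolved and onsets between T0 and discharge can still be missed.
- The intervention runs along the discharge-planning timeline, so an onset shortly before discharge is not clearly beyond its reach.
- The counting rule for incident cases may sit in an analysis plan not shown here.
- The pilot is exploratory, and its tests are declared hypothesis-generating.

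A reader might also try to size the problem from the Background's in-hospital incidence of up to one third. With an assumed 30% of caregivers still reporting it, that gives 0.33 × 0.30 = 9.9%. The documents do not support this. One third is an upper figure for hospitalised older adults generally, the 30% is invented, detection at T0 is ignored, and the result exceeds the whole expected control incidence of about 6%.

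**Conclusion.** The point holds as a contradiction to be reconciled, with a possible effect on a primary outcome. The two sections disagree on caregiver screening at T0 for the source that is normally alone on day 3. The SQiD's recall window is not anchored to discharge, and one positive report is enough for an event. Delirium that began in hospital **can** therefore be counted as post-discharge delirium. The documents do not show that it **is**.

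The size is unknown. The fall from 80% to about 69% to 53% power is an illustration that rests on 200 patients per condition, carry-over of 1% to 3% equal in both conditions and added to the planned rates, and the plan's simple chi-square comparison rather than its mixed model. It shows that small carry-over matters when the expected rates are 6% and 0.9%. It does not show an error in the stated power, which reproduces. Because the remedy is cheap and a primary outcome is affected, the change should be made even in an exploratory pilot.

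**What to change.** 1. Reconcile the Participant's timeline with the Delirium subsection, and check both against Table 1 and Fig. 4, so that the caregiver delirium screen (FAM-CAM and SQiD) is taken at T0. State at which later visits the SQiD is asked.
2. Keep the SQiD wording, so that the instrument stays comparable with its published use. After any positive caregiver report, add one question: at T1, did the change begin before or after leaving hospital; at T2 and T3, did it begin since the last interview.
3. Count a report as incident only if that source was negative at T0 or the onset is dated after discharge. State which governs when a negative T0 report is followed by an onset dated before discharge; letting the dated onset decide closes the window between T0 and discharge.
4. Keep the current any-positive definition as a sensitivity analysis.

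The cost is one short caregiver contact at enrolment, which the Delirium subsection already promises and mandatory caregiver participation makes practicable, plus one added question. The countable event rate will be lower, which matters for an outcome expected in about 6% of controls. Caregivers' dating of onset will also carry some recall error.

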**Fig. 4 Fig4:**
[figure not shown]
Study timelines. Legend: White boxes: Assessment time point in observation and intervention trial T0, T1, T2 and T3 with approximated assessment time per assessed group (patient/primary caregiver/nurse); grey boxes: intervention, process evaluation and additional data collection

### Sample size

The sample sizes for both the observational study and the pilot intervention trial were chosen based on feasibility considerations. Robust sample size estimations were not possible because of the pilot character of the study and missing preliminary information. Power analysis for the intervention study was additionally based on descriptive results from the observational part.

For the pilot study we will include 500 patients in all four study centers (125 patients each within 12 months), including an estimated dropout rate of 20%. With preliminary results of the observational study and the expected sample size of 400 (excl. drop-outs) we conducted power analyses for the primary outcomes delirium incidence and cognitive function. In the control group of the pilot intervention study we would expect an incidence of delirium of about 6% and of cognitive impairment of about 41%. Using a two-sided chi-square test at a significance level of 5% with a power of at least 80%, one should be able to show a reduction in delirium incidence in the intervention group to 0.9% and in cognitive impairment incidence to 27.7%.

Patients with an unfamiliar discharge environment and cognitive impaired patients will be preferably included, as they are the main focus of the project having a high risk of delirium.

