### Stepped wedge design

For the pilot intervention study a stepped wedge design is used [52]. All clusters start without intervention. While the first cluster starts after 12 weeks, every other cluster follows after another 8 weeks until all four clinical partners have started. Please see also Table 2.

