**Table 2 Tab2:**
[figure not shown]
Stepped wedge design and intervention entry in the pilot intervention trial. Legend: Control phase in grey parts of the table, intervention phase in blue parts of the table

During the observational study, imbalances in the distribution of participants insured by the AOK health care insurance among the different study centers were recognized. The balanced allocation of AOK health care insurance holders is an important feature for health economic evaluation. To minimize these imbalances for the pilot intervention study, a pre-defined cluster entry as given in Table 2 was chosen rather than a randomized approach.

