### Statistical analysis

The data of the observational study will be analyzed by descriptive statistical methods and regression analyses for demographic aspects as well as for the main outcomes.

Regarding the pilot intervention study descriptive analyses and mixed models (with logit-link for binary outcome and identity-link for continuous outcome) according to Thompson et al. and Goldfeld will be conducted to account for the stepped wedge design [53, 54]. To account for missing values, we will use multiple imputation methods or sensitivity analyses [55].

Analyses will be done in total as well as stratified by study centers. Subgroup analyses for known and unknown discharge environments as well as for cognitive fit and impaired patients are planned. Statistical tests will be two sided with a 5% level of significance. Because of the explorative character of the study no adjustment for multiple testing will be done. All results of statistical tests will be interpreted as hypothesis generating and not as a statistical proof. The software Statistical Analysis Software (SAS) and R will be used for analyses.

The health economic evaluation includes patients from both the observational and interventional part. Cost and cost-effectiveness analyses will be carried out in a difference-in-differences approach including subgroup analyses (e.g. based on age, gender or cognitive status). Sensitivity analyses will be also being performed.

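### The 80% power statement is computed for a plain two-group chi-square test, not for the four-centre stepped-wedge analysis; with time adjustment, power for the same effects is about 30–41%

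*Protocol article*

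**What the plan says.** The Sample size section says that both sample sizes rest on feasibility and that robust estimation was not possible. It then gives a power analysis for the pilot trial, based on 500 recruited, 20% dropout and so 400 completers. For the control group, "we would expect an incidence of delirium of about 6% and of cognitive impairment of about 41" per cent. The power sentence begins "Using a two-sided chi-square test at a significance level of 5% with a power of at least 80%, one should be able to show" and ends with "a reduction in delirium incidence in the intervention group to 0.9% and in cognitive impairment incidence to 27.7" per cent. No ICC, period effect, centre effect or design effect is mentioned.

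The Stepped wedge design section describes four clusters that all begin in the control condition: "While the first cluster starts after 12 weeks, every other cluster follows after another 8 weeks until all four clinical partners have started". The order of entry is not random: "a pre-defined cluster entry as given in Table 2 was chosen rather than a randomized approach".

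The Statistical analysis section plans mixed models, with a logit link for binary and an identity link for continuous outcomes, which "will be conducted to account for the stepped wedge design". It does not list the time or centre terms. It also says that tests are to be read as hypothesis generating.

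**The concern.** The power figure belongs to a different design from the one being run. A two-group chi-square test treats the 400 completers as independent patients allocated side by side. In a stepped wedge with one-way crossover, control patients come mainly from early calendar time and intervention patients mainly from late calendar time. Once the model adjusts for period, only periods in which some centres have crossed over and others have not carry direct information on the treatment effect. Much of the precision is lost even with no true variation between centres.

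At stake is how the pilot's result is used. The article presents the pilot as the foundation for a confirmatory study and says it will show whether the intervention can have an effect. A planner who takes the stated detectable effects at face value would overrate the precision of the pilot estimate and could give a non-significant result more weight than it can bear.

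**Working it through.** **Inputs from the article.** Two-sided α = 0.05; 400 completers, 100 per centre; control rates 6% and 41%; intervention rates 0.9% and 27.7%; crossovers at weeks 12, 20, 28 and 36; recruitment over 12 months.

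**Assumptions.** Period lengths of 12, 8, 8, 8 and 16 weeks (52 in total; Table 2 is not shown); even recruitment; categorical period effects in the model; ICC from 0 to 0.05. The 200:200 split is not stated either, but is inferred because it reproduces both figures.

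**Step 1. Reproduce the stated figure.** Power = Φ[(|p₁ − p₂| − 1.96·s₀)/s₁], with s₀ = √(2·p̄(1 − p̄)/n), s₁ = √([p₁(1 − p₁) + p₂(1 − p₂)]/n) and n = 200.

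- Delirium: p̄ = 0.0345, s₀ = 0.01825, s₁ = 0.01807. Power = Φ[(0.051 − 0.03577)/0.01807] = 80.0%.
- Cognitive impairment: p̄ = 0.3435, s₀ = 0.04749, s₁ = 0.04702. Power = Φ[(0.133 − 0.09307)/0.04702] = 80.2%.

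Both agree with the article. A continuity correction would give 71% and 77%, so it was not used. The schedule's own 46:54 control-to-intervention split changes little (80.7% and 80.1%).

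**Step 2. Variance with period effects only, ICC 0.** Within a period, the information is N_j·f_j(1 − f_j), where f_j is the fraction of centres on intervention: 0, ¼, ½, ¾ and 1 in the five periods. The first and last periods contribute nothing, yet hold 28/52 = 54% of the patients. Each 8-week period holds 400 × 8/52 = 61.5 patients. The total is 61.5 × (0.1875 + 0.25 + 0.1875) = 38.46. The variance factor is 1/38.46 = 0.0260, against 2/200 = 0.0100 for the plain comparison, so the inflation is **2.6**.

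**Step 3. Other models on the same layout** (generalised least squares, 4 centres × 5 periods). Power uses the Step 1 formula with n = 200/inflation.

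| Model | Inflation | Power, delirium | Power, cognitive impairment |
|---|---|---|---|
| Period effects, ICC 0 | 2.6 | 41% | 41% |
| Period effects, random centres, ICC 0.01 | 3.0 | 36% | 36% |
| Period effects, random centres, ICC 0.05 | 3.3 | 33% | 33% |
| Fixed centre and period effects | 3.8 | 30% | 30% |

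Example for cognitive impairment with inflation 2.6: s₀ = 0.04749 × √2.6 = 0.0766 and s₁ = 0.04702 × √2.6 = 0.0758. Power = Φ[(0.133 − 0.1501)/0.0758] = 41%.

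The 95% half-width for the risk difference in cognitive impairment, 1.96·s₁, goes from 9.2 percentage points in the plain comparison to 14.9 (inflation 2.6) or 17.9 (inflation 3.8). The planned difference is 13.3 points.

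**Step 4. Completers needed for 80% power on this layout.** 400 × 2.60 = 1,040 with period effects only; 400 × 3.76 ≈ 1,500 with fixed centres as well. These figures show the size of the gap and are not a proposal.

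**Step 5. Sensitivity.**

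- Method: logistic likelihood-ratio simulation (1,500 runs per case) gives 48% (period) and 40% (period and centre) for delirium, and 41% and 31% for cognitive impairment. Risk-difference, logit and simulation variants together span 29–48%.
- Linear time trend instead of categorical periods: 44–46% without and 33–37% with centre effects.
- Layout: ending at week 44 gives 40–51% (period) and 32–41% (period and centre). Five equal periods give 43–55% and 33–43%.
- No time terms at all: about 67–80%.

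**The case against.** The article names its method, the arithmetic is right for that method, and it never says that the mixed model has 80% power. That stands: this is a mismatch between the power test and the planned analysis, not a calculation error.

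The article also says that the sample is feasibility-based, that robust estimation was not possible and that tests are hypothesis generating, and it leaves effectiveness to later confirmatory studies. That excuses a small sample and lowers the severity. It does not make the two stated detectable effects correct for this design.

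The strongest technical objection is that period terms are not listed, and nearly all of the loss comes from them. This is fair, and it makes the figures conditional. But omitting time terms would confound the intervention with calendar time, in a trial with a fixed entry order whose start had already been postponed because of the pandemic. Time adjustment is the only sensible reading of accounting for a stepped wedge.

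Finally, the cognitive figure concerns a dichotomised outcome. MoCA is measured at baseline, day 7 and day 90, and an identity-link model is planned for continuous outcomes, which may be more precise. A reader might infer that about 30–41% is the trial's power for cognition in general; the documents do not support that.

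**Conclusion.** The point holds as a mismatch between power calculation and analysis that should be fixed. The stated 80% applies to 200 versus 200 independent patients. Under a stepped-wedge model with period adjustment, 400 completers and a 12/8/8/8/16-week schedule, the variance is about 2.6 to 3.8 times larger, and power for the same binary effects is about 30–41% by normal approximation, or 29–48% across methods. With time adjustment, no layout or method tried exceeded 55%. The delirium figures are the rougher ones, since only about 2 events are expected in the intervention phase (0.9% of about 215 patients). Small-sample corrections for four centres would lower power further.

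Stronger readings that a reader might infer are not supported:

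- That the trial has one definite power figure. It depends on Table 2 and on model terms that the article does not give.
- That the loss arises wholly before any centre effect enters. The low end comes from a model with centre terms, even where the true ICC is zero.
- That the trial is invalid or must enrol more. Its size does not rest on the power figure.
- That the power to abolish delirium, or to match the pooled reduction cited in the Background, can be read off. The first strains the normal approximation with no intervention-phase events. The second is ambiguously worded and is not a planning input.

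**What to change.** Replace the power sentence with power, or preferably expected confidence-interval width, computed under the stepped-wedge model. Use the actual Table 2 periods, state the period and centre terms, and show an ICC range of 0 to 0.05. If 0.9% and 27.7% are kept, label them as an unadjusted individual-level approximation that overstates power under the planned analysis. Say that the cognitive figure refers to the dichotomised outcome and not to a continuous MoCA analysis. Leave enrolment unchanged.

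The cost is rewording and a short calculation. The stated figure becomes less favourable; nothing in the conduct of the trial changes.
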